## 1. Background:

Food insecurity is defined as limited or uncertain access to nutritionally adequate, safe, and acceptable foods due to financial resource constraint. Over fourteen million, or eleven percent, of U.S. households were food insecure at some time during 2018. Rates of food insecurity in 2018 were higher than the national average for households with children, specifically children under age 6 (14.3%) and in low-income households. Food insecurity in children is associated with increased risks of lower nutrient intake, cognitive problems, anemia, asthma, aggression and anxiety as well as risk of being hospitalized and reporting being in fair or poor health. Additionally, it may exacerbate the onset or persistence of other adverse health conditions, including overweight and obesity.

One protective factor against food insecurity is child participation in preschool programs, such as Head Start (HS), and participation in summer programs. HS promotes school readiness for children in low-income families by offering educational, nutritional, health, social, and other services to over 1 million children each year nationwide. Also, Head Start and full-day summer programming promotes food security by providing free breakfast and lunch. Participants are from low-income families with the majority of families representing racial/ethnic minorities. Food security improves both health and learning in childhood, however, there are no program regulations for routinely assessing or responding to food insecurity among HS and summer parks and recreation families. In Davidson County, the Metro Action Commission provides food during the school year for HS children and for summer parks and recreation programs that reach hundreds of underserved children who can lack access to food during the summer months. Moreover, while all these meals meet USDA requirements, often food provided can include foods with high added sugar with high total calories and can be wasted.

The “Food for Thought” study will leverage the Nashville Collaborative, a well-established community-academic partnership led by [name], that addresses childhood obesity and the social, economic and policy-based structures associated with health disparities in obesity, including food security. Our Community Advisory Board (comprised of 15 organizations including Head Start, Parks and Recreation, the United Way, and the Nashville Public Library) recognized food security as a fundamental need for children and endorsed the project. Utilizing a Nashville Collaborative previously tested project to build cooking skills for children and parents, we will work with our community partners to design an alternative way to deliver this cooking skills program.

**Due to the COVID-19 pandemic, this issue has gained even more importance. Food insecurity has increased substantially with children out of school and without in-person programming that typically would have provided breakfast and lunch. To this is the added challenge of maintaining physical distancing and ensuring the safety of underserved families who have been hit the hardest. Due to this unprecedented circumstance, the Food for Thought Steering Committee along with the Nashville Collaborative Advisory Committee, representing more than 15 different community agencies, have guided us to revise our Food for Thought grant aims. We summarize**

these revised methods to continue to the same overarching goal of Food for Thought, examining how we can maximize good nutrition that is economically sustainable and influences larger related policies.

## 2. Study Aim:

Develop and test programs to measurably improve family health upon two rigorously tested programs adapted to the COVID-19 context. This will be done by delivering an adapted Teaching Kitchen Outreach program^8 (weekly groceries and recipe videos) as well as testing an adapted Healthier Families program (an evidence-based 12-week health coaching intervention).

## 3. Study Hypothesis:

All parent-child dyads who participate in the study will have improved family health post-intervention. They will also exhibit improvements in all other outcomes measured (food security, parent and child nutrition, family resilience, etc.). Participants in the intervention group will demonstrate augmented improvements in these outcomes compared to the control group.

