## 6. Study Design, Procedures, and Schedule of Events for Study Participants

Research activities will include surveys administered by trained key study personnel to measure participant demographics, maternal-child health, family coping, specifically in relation to COVID-19, and family health. Please reference Table1 for additional details including the process measures that will be recorded. All data, including data referencing a child, will be collected directly from the parent or guardian. This will include a total of 2 surveys, with one to be administered pre and post study activities. The intervention will be conducted with families of children participating in various community programs and/or receiving care from providers in the Vanderbilt Department of Pediatrics. The goal of this study is to conduct a randomized clinical trial to test the effect of two evidenced based programs (Healthier Families and Teaching Kitchen Outreach [TKO]) adapted to a virtual platform on improving family health.

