| Family Health                            | The Family Health Scale developed by Crandall et al. was used to measure global family health. The survey includes four subscales: 1) family social and /emotional health processes, 2) family healthy lifestyle, 3) family health resources, and 4) family external social supports and a short form to measure global family health. Our study includes the validated 32-item long-form version of the FHS.                                                                                                                          |
| Parent and Child General Health          | This component of the survey will be included to ask the participating parent's views on their own as well as their child's general health. We will solely include the first item found on the validated SF-12 Health Survey to assess this construct. We ask the question twice, though we will adapt the second iteration to reference the index child's health.                                                                                                                                                                                  |
| Nutrition                                | To assess the index parent's food and drink intake, we will include the brief eight-item Starting The Conversation (STC) Scale developed by Paxton, et al.  This survey has been validated in previous literature and no adaptations will be made. To assess child nutrition, the longer, in-depth Child Dietary Screener developed by the Centers for Disease Control will be used.                                                                                                                                      |

|                                      |                                                                                                                                                                                                                                                                                                                                                                                                                                                                                                                     |

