| COVID-19 Impact                      | To understand the extent to which index parents and their children are exposed to the impact of the COVID-19 pandemic, we will include the COVID-19 Exposure and Family Impact Scale (CEFIS) developed by Kazak, et al. This scale has been tested and validated by previous research studies. Part 3 of the CEFIS will be excluded from our survey.                                                                                                                                                   |

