## **12. Adverse Events or Unanticipated Problems Involving Risk to Participants:**

The principal investigator and research staff (with oversight by the principal investigator) are responsible for ensuring protocol compliance, data integrity, and participant safety. This protocol presents minimal risks to participants and adverse events or other problems that are not anticipated. All suggested dietary changes are evidence-based and healthy. We expect tangible benefits to accrue to all subjects of the study: participants are expected to experience improved nutrition and health as a result of participating in the study. If any physical injury or illness should occur as a direct result of participation in this study, Vanderbilt University Medical Center maintains limited research insurance coverage for the usual and customary medical fees for reasonable and necessary treatment of such injuries or illnesses. The informed consent document will include this statement and will provide pertinent contact information. In the unlikely event that such events occur, unanticipated problems involving risks to subjects or others will be reported immediately to the principal investigator and to the IRB and in writing within 7 days. While this study is not a federally funded research project (funded by the Joe C Davis Foundation), the study team will report any action resulting in the temporary or permanent suspension of this study to the donor responsible for the gift funding this study

377 **13. Proposal Process to Date:**

- 378
- 379 • Initial application submitted to the Vanderbilt University Medical Center (VUMC)
  - 380 Institutional Review Board (IRB) submitted on February 7, 2020
  - 381 • IRB approval obtained March 12, 2020
  - 382 • Final revision to IRB application on June 24, 2021
  - 383 • Clinical trials registration submitted March 25, 2022
  - 384 • Clinical trials registration approved on April 13, 2022. Assigned ClinicalTrials.gov
  - 385 Identifier: NCT05328193
- 386
- 387
- 388
- 389
- 390
- 391
- 392
- 393
- 394
- 395
- 396
- 397
- 398
- 399
- 400
- 401
- 402
- 403
- 404
- 405
- 406
- 407
- 408
- 409
- 410
- 411
- 412
- 413
- 414
- 415
- 416
- 417
- 418
- 419
- 420
- 421
- 422

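### Family health leads the protocol, but no score or between-arm test is named primary, while improvement is predicted on every measured outcome

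*Protocol*

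**What the plan says.** Family health is the only health target in the aim (Section 2): "Develop and test programs to measurably improve family health upon two rigorously tested programs adapted to the COVID-19 context". Section 6 repeats it as the goal of the trial, which tests two programmes "adapted to a virtual platform on improving family health".

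Section 3 makes three predictions in order:
- For everyone in the study: "All parent-child dyads who participate in the study will have improved family health post-intervention".
- For the rest of the survey: "They will also exhibit improvements in all other outcomes measured (food security, parent and child nutrition, family resilience, etc".
- For the randomised contrast: "Participants in the intervention group will demonstrate augmented improvements in these outcomes compared to the control group".

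In Table 1 the Family Health row describes four subscales and a short form, then settles the instrument: "Our study includes the validated 32-item long-form version of the FHS". It does not say whether the total or the subscales are the analysed score.

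Section 9 plans paired t-tests within groups and two-sample t-tests between groups for the change from baseline to 12 weeks, with Tobit models for markedly skewed scales. It refers to outcomes collectively. It ranks neither the outcomes nor the two kinds of comparison, and it gives no significance level.

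**The concern.** A randomised trial needs one comparison, fixed in advance, that decides whether the intervention worked. Here the lead construct is clear but the deciding test is not, in three respects:

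- **Which score.** The 32-item total and the four subscales are all available.
- **Which comparison.** The leading sentence of the hypothesis concerns improvement in all participants, which is a before-after statement. Under Section 6 both arms receive recipe videos and groceries, so change within an arm cannot show what coaching adds. Only the between-arm test can, and Section 9 gives it no priority.
- **Which outcome if family health is null.** Because improvement is predicted on everything measured, a significant difference on any one score could be presented as confirming the hypothesis.

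The stake is a headline result chosen after the data are seen, with a false-positive risk well above the level a reader would assume.

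**Working it through.** The protocol states no significance level, number of tests or error rate, so it has no figure of its own to reproduce.

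**Step 1: count the scores in Table 1.** Resilience 1, family health 1, general health 2 (parent, child), nutrition 2 (parent, child), sleep 2 (parent, child), food patterns 1, food security 1. The sum is 10. Scoring the two food-pattern sources separately, or adding the COVID-19 scale, gives 11; doing both gives 12. Counting one score per table row gives 7, or 8 with COVID-19. Demographics are excluded throughout.

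**Step 2: chance of at least one false between-arm positive.** Assumptions: two-sided 5% per test, no true difference between arms on any score, and any single significant result counts as success. For k independent tests the chance is 1 − 0.95^k. For k = 11 this is 1 − 0.95^11 = 0.431. For correlated scores, 200,000 sets of normal test statistics with equal pairwise correlation were simulated.

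| Scores | Independent | 0.3 | 0.5 | 0.7 |
|---|---|---|---|---|
| 7 | 30% | 27% | 23% | 18% |
| 8 | 34% | 30% | 25% | 19% |
| 10 | 40% | 35% | 29% | 21% |
| 11 | 43% | 37% | 30% | 22% |
| 12 | 46% | 40% | 32% | 23% |

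A single named test gives 5%. The smallest entry, 18%, is more than three times that.

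**Step 3: family health alone.** Even if only family health could decide the trial, four subscales tested separately give 1 − 0.95^4 = 0.185 if independent, and less if positively correlated. So naming the construct without the score does not bring the risk to 5%.

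**Step 4: why one named test is better than correcting all of them.** Assume 1:1 allocation of the maximum 200 dyads and no dropout, so 100 per arm. The difference detectable with 80% power is (1.96 + 0.84) × √(2/100) = 0.40 SD. Bonferroni over 11 tests uses 0.05/11 = 0.00455 each and needs about 0.52 SD. Power at 0.40 SD falls from 81% to 50%.

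**Step 5: dates, as a side check.** Section 4 plans recruitment through May 2021, Section 8 allows up to 30 days before randomisation, and Section 7 gives a 12-week follow-up. 31 May 2021 + 30 + 84 days = 22 September 2021. Section 13 records: "Clinical trials registration submitted March 25, 2022".

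**The case against.** The strongest reply is that the protocol does have a lead outcome. Family health comes first in three sections, and the 32-item form is fixed as the instrument. That stands: a reader might infer that all outcomes carry equal weight, or that the short form is still a candidate, and the text supports neither. What it lacks is the primary label, the choice between total and subscales, and priority for the between-arm test.

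A second reply is that predicting improvement on all outcomes, if read as requiring all of them, does not inflate the error rate. That is correct. Inflation arises only if any single success counts. The protocol gives no decision rule in either direction, so the figures are conditional on that reading.

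A third is that multiplicity adjustment and testing order may be set in a separate SAP that is not at hand. That also stands, and the absence of an adjustment is not the point here. The choice of primary outcome belongs in the protocol.

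A reader might also multiply 11 scores by three tests (one within each arm, one between arms), get 33, and quote 1 − 0.95^33 = 82%. The documents do not support this. Depending on how Table 1 is counted, the number of tests runs from 21 to 36. The three tests per score share data, and allowing for that gives about 74% with uncorrelated outcomes and 44% at correlation 0.7. Moreover, no change within either arm is an implausible null when both arms receive the food programme.

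Two further inferences go too far. Demographics appear in the outcome table, but Section 9 handles descriptive variables separately, so this is a labelling matter. The COVID-19 scale is introduced with "To understand the extent to which index parents and their children are exposed to the impact of the COVID-19 pandemic", but it also measures family impact, which could change. Late registration does not show that the choice of outcome was driven by data: the September 2021 date rests on planned recruitment, and Section 8 mentions a first cohort, which leaves room for later, undated ones.

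**Conclusion.** The concern holds in this form. Family health is the lead construct, but no outcome or score is designated primary, the hypothesis covers every measured outcome, and Section 9 does not say whether a within-arm or a between-arm result decides the trial. With about 11 between-arm tests the chance of at least one false positive is roughly 43% if independent and 22% at correlation 0.7, against 5% for one named test. This rests on three assumptions: a two-sided 5% level, which the protocol does not state; the count of scores in Step 1; and success being claimable from any single significant result. The defect should be corrected, and it is cheap to correct. The labelling of Table 1 and the registration date are side remarks and do not carry the conclusion.

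**What to change.** In Sections 3, 6 and 9, name one primary test: the between-arm comparison of the 32-item Family Health Scale total at 12 weeks, adjusted for its baseline value, with its significance level stated. The baseline score is already collected, and adjusting for it deals with chance imbalance at no extra burden. Label the within-arm changes, the four subscales and all other Table 1 scores secondary or exploratory, give them 95% confidence intervals, and report all of them.

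As side remarks, list demographics and the exposure part of the COVID-19 scale as descriptors, and note that registration came after the planned end of follow-up, if the planned dates held. The protocol text records events in April 2022, so it should also state when the primary test was chosen and whether outcome data had been seen by then.

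The cost is wording only, with no new data or visits. The downside is that secondary results can no longer be claimed as confirmatory.

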## 4. Study Population and Sample Size:

In this randomized clinical trial, rolling recruitment will occur for approximately months starting in February of 2021 and running through May of 2021 until up to 200 participating parent-child dyads that fit the eligibility inclusion criteria as outlined below have been identified. Eligible participants whose providers have given permission will be contacted by key study personnel through email, text, or phone calls to invite them to participate in a study using a standard script. We will continue to contact eligible patients until we reach our recruitment goal. Participants will be recruited from the Vanderbilt Pediatric Primary Care Clinic or Nashville Collaborative community partner sites. This study will serve underserved populations, with limited access to financial resources. Low-income households, single-parent households, and households headed by Black or Latino adults - groups historically impacted by health disparities - experience a higher prevalence of food insecurity and reduced access to healthy foods, and they are thus appropriate targets for this study. These are also the populations that primarily comprise the populations served by Head Start, Parks and Recreation, Nashville Public Library, Project Transformation, Martha O'Bryan, and St. Luke's. Of those participants that meet eligibility and are enrolled in the study, all potential benefits and burdens are distributed fairly.

## 5. Screening and Enrollment:

Parents will be identified by 1 of 2 processes. This will vary based on whether said potential participants are eligible to participate due to involvement with specific community partners or due to being a current patient of the Vanderbilt Primary Care Pediatrics Clinic.

## 1) Community Organization Procedure

Research staff will not be initiating contact with any participants from community partners. Community partners will share study contact information to allow interested families to contact KSP if they are interested. Partners are unable to provide a list of patron names without compromising confidentiality and their relationships with the families they serve. Partners will share our information only and will not conduct recruitment activities directly.

## 2) Vanderbilt Primary Care Pediatrics Clinic Procedure

Appropriately trained key study personnel will pre-screen patient-families by pulling electronic medical records from Epic (eStar). Parents who are contacted will also complete an eligibility screen in REDCap either verbally (with study personnel over the phone) or electronically (on their own using a computer or cell phone with internet access).

Parents and their children will be assessed for eligibility prior to informed consent and baseline data collection. Trained and certified data collectors will determine an interested parent-child dyad's eligibility according to the following criteria:

### *Parent eligibility inclusion criteria:*

- Currently participating in programming with one of the involved community partners, including, Parks and Recreation, Nashville Public Library, Project Transformation, Head Start, Martha O'Bryan, and St. Luke's; Patients who receive primary care at the Vanderbilt Primary Care Pediatrics Clinic are eligible as well.
- Community partners will share study contact information to allow interested families to contact KSP if they are interested.
- Partners are unable to provide a list of patron names without compromising confidentiality and their relationships with their families. Partners will share our information only and will not conduct recruitment activities directly.
- Parent/legal guardian age  $\geq 18$  years
- Parent legal guardian of a child ages 3-8
- Ability to participate on a virtual platform (such as Zoom, FaceTime, What's App, Google Hangouts)
- Ability to attend a Zoom tool training and complete a baseline survey prior to programming
- Be able to access virtual programming through online platforms, including YouTube
- Speak English or Spanish

### *Parent eligibility exclusion criteria:*

- inability to complete data collection measures via telephone, Redcap, or paper measures
- language other than English or Spanish

## 6. Study Design, Procedures, and Schedule of Events for Study Participants

Research activities will include surveys administered by trained key study personnel to measure participant demographics, maternal-child health, family coping, specifically in relation to COVID-19, and family health. Please reference Table1 for additional details including the process measures that will be recorded. All data, including data referencing a child, will be collected directly from the parent or guardian. This will include a total of 2 surveys, with one to be administered pre and post study activities. The intervention will be conducted with families of children participating in various community programs and/or receiving care from providers in the Vanderbilt Department of Pediatrics. The goal of this study is to conduct a randomized clinical trial to test the effect of two evidenced based programs (Healthier Families and Teaching Kitchen Outreach [TKO]) adapted to a virtual platform on improving family health.

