### Process Measures:

Process measures will be recorded for each scheduled session of the health coaching intervention and will also include TKO recipes prepared, session duration, modules completed, goals set, progress on goals, and parent and child health coach session attendance. Health coaches will record process measures following each scheduled session, regardless of whether the session was successfully completed (i.e., parent-child dyad canceled, rescheduled, or did not show for the session).

Both the intervention and control condition will receive up to 12 weekly short (about 2-3 minutes) TKO videos. Recipe specific groceries will be delivered to participants' homes by a third-party grocery delivery company or will be available for pickup at a central location(s). Please reference Table 2 to see the recipes that will be provided as part of this intervention. These recipes reflect foods that can be purchased with SNAP and WIC and include tested meals and snacks that were developed and evaluated in person in Parks and Recreation after-school programming (Heerman W, Elsakary Y, Sommer E, Escarfuller J, Barkin S. Assessing the Scale and Spread of an Experiential Teaching Kitchen in After-School Programming Among School-Aged Children) through the long-standing Nashville Collaborative partnership (<https://www.childrenshospitalvanderbilt.org/program/nashville-collaborative>). Over more than a decade, we have developed and tested programs together to improve health and wellness and reduce childhood obesity in our community.

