| 10. Black Bean and Corn Salad   | 
 
• 2 cans of corn (no salt added)
 
• 1 large cucumber or 2 small cucumbers
 
• 1 bunch of chives
 
• 1 can of black beans (no salt added)
 
• 1 bag of corn tortillas (not chips)
 
• 1 container of cumin
 
                                                                                                                          |
| 11. Build Your Own Banana Split | 
 
• 5 large bananas
 
• 1 large container of Greek yogurt, plain, nonfat
 
• 1 container of blueberries
 
• 1 container of blackberries
 
• 1 container of raspberries
 
                                                                                                                                                                       |

Those randomized to the intervention condition will also receive a 12-weekly health coach via a virtual platform (such as Zoom, FaceTime, or What's App) to provide an adapted version of the previously tested Healthier Families program. Adaptations include shortening each session to 30 minutes and delivering the programming via a virtual platform. The health coach will provide the Healthier Families modules (refer to Table 3) either to individual child-parent pairs or with groups of parents (virtual group visit model). Participants will be encouraged to share pictures or videos of what they are learning and applying in their families related to the modules (e.g., recipes, cooking, physical activity). To do this, platforms such as Facebook might be used. If Facebook will be used in any form or fashion, it will be completely voluntary, and participants will be made aware that it is not a secure platform. This will be included in the consent and will be emphasized when the programming

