**8. Randomization:**

Randomization will occur after obtaining informed consent as well as the completion of certain baseline data collected by the parent (i.e., the baseline survey). This process will be completed within a maximum of a 30-day period. Once successfully completed, randomization will occur. Within the first cohort of the trial, parent-child dyads will be grouped according to parent preferred language (English versus Spanish), resulting in two strata within each region. Dyads within the strata will be randomized to the intervention and control groups within each of the two regions for a total of up to 200 parent-child dyads. Participants will be randomized by an unblinded KSP. Participants will be told which group they were randomized to.

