**9. Statistical Analysis Plan:**

We will describe participant characteristics using mean (standard deviation [SD]) or frequency (percentage), as appropriate. Comparison of descriptive variables between the control group and intervention group will be performed using a chi-squared test for categorical variables and a 2-sample, independent t-test for continuous variables. We will test for changes between baseline and 12-week follow-up outcomes using paired t-tests for within group comparisons. We will test for changes between baseline and 12-week follow-up outcomes using 2-sample, independent t-tests for between-group comparisons of the intervention and control group. We will conduct Tobit regression models for scales in which there is a considerable degree of skewed data.

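### Both arms receive Teaching Kitchen Outreach, so the randomised comparison can test only the added coaching, and the within-arm paired tests cannot separate programme effect from time

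*Protocol*

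**What the plan says.** Section 6 sets the goal of the randomised trial as to "test the effect of two evidenced based programs (Healthier Families and Teaching Kitchen Outreach [TKO"]), both adapted to a virtual platform, with family health as the target.

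The same section describes what each arm gets:

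- **TKO videos:** "Both the intervention and control condition will receive up to 12 weekly short (about 2-3 minutes) TKO videos".
- **TKO groceries:** "Recipe specific groceries will be delivered to participants' homes by a third-party grocery delivery company", or can be collected at a central place. No arm is excluded, and Section 7 likewise promises the ingredients to participating parents generally.
- **Coaching:** after Table 2, "Those randomized to the intervention condition will also receive a 12-weekly health coach via a virtual platform".

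Section 8 has two groups: "Dyads within the strata will be randomized to the intervention and control groups within each of the two regions". Neither is without TKO.

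Section 3 makes two separate predictions. The first is that "All parent-child dyads who participate in the study will have improved family health post-intervention". The second is that improvement will be larger in the intervention group than in the control group. Section 9 plans tests of change from baseline to 12 weeks "using paired t-tests for within group comparisons" and two-sample t-tests between the groups. Section 6 allows two surveys per participant, one before and one after.

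**The concern.** A randomised trial can test a programme only if the arms differ in receiving it. Here they differ in coaching alone, so the goal in Section 6 claims more than the design can deliver.

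The first prediction in Section 3 has no control group behind it. The only planned analysis that fits it is the paired test within each arm, although the protocol does not say so outright. The protocol also gives reasons to expect change over the study period without any programme: Section 1 says that food access for underserved children can fall in summer and that food insecurity rose with the pandemic. Food security is one of the outcomes in Section 3. A significant change within an arm, read against the Section 6 goal, could be credited to TKO when the data cannot show that.

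**Working it through.** The protocol gives no alpha, SD, effect size or allocation ratio behind its maximum of 200 dyads, so there is no figure to reproduce. The check is structural, followed by an illustration.

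**1. What each contrast estimates.** Let T be the mean change due to TKO, H the further change due to coaching when TKO is also given, and s the change that 12 weeks would bring anyway.

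- Control arm: mean change = T + s
- Intervention arm: mean change = T + H + s
- Between arms: (T + H + s) − (T + s) = H
- Paired test, control arm: T + s
- Paired test, intervention arm: T + H + s

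T cancels from the only randomised contrast. Two surveys give one change per dyad, so T and s cannot be separated within an arm.

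**2. Between-arm test.** Assumptions not in the protocol: two-sided alpha 0.05, 1:1 allocation, 100 per arm, effects in SD of the change score. In 20,000 simulated trials per setting:

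| T | H | s | Mean difference | Two-sample test rejects |
|---|---|---|---|---|
| 0 | 0 | 0 | 0.00 | 5.2% |
| 0.3 | 0 | 0 | 0.00 | 4.8% |
| 0.6 | 0 | 0 | 0.00 | 5.1% |
| 0.3 | 0.4 | 0 | 0.40 | 80.2% |
| 0 | 0.4 | 0.3 | 0.40 | 80.3% |

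The test rejects at alpha whatever T is, and responds to H whatever T and s are. The normal formula agrees for H = 0.4: 0.4 × √(100/2) = 2.83; 2.83 − 1.96 = 0.87; power about 81%.

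**3. Calendar.** Section 4 places recruitment in February to May 2021, and Section 7 places follow-up at 12 weeks (84 days). Counting 84 days from 1 February gives 26 April, and from 31 May gives 23 August. Follow-up therefore falls roughly from late April to late August, later by however much of the 30 days allowed in Section 8 is used before randomisation.

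**4. Paired test with no programme effect (T = H = 0).** The rejection rate is P(|t| > critical value), with t noncentral on n − 1 degrees of freedom and noncentrality (drift in SD of change) × √n. For n = 100 and drift 0.2, the noncentrality is 0.2 × 10 = 2.

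| Drift s | 100 per arm | 80 per arm (20% loss) |
|---|---|---|
| 0.1 | 17% | 14% |
| 0.2 | 51% | 42% |
| 0.3 | 84% | 76% |

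**5. Programme and time look alike.** Simulated control-arm paired tests, 100 per arm:

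- T = 0.3, s = 0: 84.5%
- T = 0, s = 0.3: 84.7%
- T = 0.15, s = 0.15: 84.5%
- T = 0.3, s = −0.3: 5.3%

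The first three cannot be told apart. In the last, a real TKO effect is hidden.

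**The case against.** The strongest reply is that the design is sound and one sentence is loose. Section 2, although it opens by speaking of testing programmes in the plural, goes on to say that TKO is delivered and Healthier Families tested. Section 3 closes with the correct between-arm prediction, and Section 9 tests it directly. A TKO effect or time trend common to both arms cancels there. All of that stands, and it limits how serious the point is. It also stands that a paired t-test is valid for the literal statement that a mean changed.

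Several stronger readings are tempting, and the protocol does not support them:

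- **That the paired tests measure only calendar time.** They measure programme and time together. The direction of the bias is unknown: loss of summer meals could worsen outcomes, and easing of the pandemic could improve them.
- **That the trial will announce that TKO works.** Section 9 attributes no change to TKO, and Section 3 does not name it as the cause.
- **That a coaching effect will be inferred because one arm's paired test is significant and the other's is not.** Section 9 specifies a two-sample comparison, and nothing says that the paired p-values will be set side by side.
- **That regression to the mean inflates the changes.** This needs selection on an extreme baseline value, and Section 5 sets no threshold on food security, family health or any other score.
- **That TKO uptake in the control arm is certainly unmeasured.** Section 6 says "Health coaches will record process measures following each scheduled session" and counts recipes prepared among those measures, with no control-arm counterpart described. But the survey's food-behaviour items are not listed one by one, so the gap is probable rather than proven.

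**Conclusion.** The concern holds in limited form. The Section 6 goal of testing TKO in this randomised trial cannot be met, because no arm goes without it. This conclusion needs no assumption about effect size or sample size. The prediction that all dyads improve can be addressed only by uncontrolled before-after tests, which do not identify a programme effect.

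The 17% to 84% range illustrates how readily such a test turns significant from drift alone. It rests on the assumed drift of 0.1 to 0.3 SD of change, two-sided alpha of 0.05 and 100 dyads analysed per arm. It is not an estimate of what happened in 2021.

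The randomised test of coaching, the randomisation and the sample size are untouched. The correction is worth making, but it does not threaten the main comparison.

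**What to change.** 1. In Section 6, state the goal as the effect of adding Healthier Families coaching to TKO, compared with TKO alone, in line with the distinction that Section 2 draws between delivering one programme and testing the other.
2. In Sections 3 and 9, make the between-arm contrast the sole basis for efficacy claims.
3. Label the within-arm changes descriptive, report them as means with 95% confidence intervals, and do not attribute them to TKO.
4. Optionally, add one item on the number of TKO recipes prepared to the 12-week survey in both arms, so that uptake can be compared.

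The cost is wording in three sections and, if wanted, one survey question. No sample size or between-arm analysis changes. The real price is that a claim of efficacy for TKO is given up, and this design could not have supported one.
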